## Methods: Data collection, management, analysis

### Data collection methods

All data will be registered in specific case report form including neonatal demographic data, prenatal and perinatal history and morbidity profiles of both mother and newborn. Hemodynamic parameters, diuresis and respiratory parameters will be continuously monitored during the first 3 weeks of treatment. Biochemical parameters, such as a complete blood count, serum electrolytes levels, renal and liver function tests will be measured before starting treatment (T0) and once a week for the first 3 weeks of treatment (T7, T14, and T21). Electrocardiogram and echocardiogram will be performed before starting treatment and once a week for 3 weeks of treatment. Any drugs that are concomitantly administered and procedures performed will be recorded.

To investigate the safety of propranolol 0.2% eye micro-drops treatment, the concentration of propranolol will be measured on dried blood spots using the liquid-chromatography tandem-mass spectrometry test [68, 69] at the steady state on the 10th day of treatment, before administering therapy (T0), after 2 (T2), 4 (T4) and 6 h (T6). Additionally, parents will be asked to consent to us taking and storing 0.3 ml of plasma.

The stage of ROP disease should be established by complete ophthalmological evaluations, planned according to ROP Guidelines [3, 66, 67], also considering the progression and the severity of ROP. The ophthalmologic exam should verify the absence of local adverse events due to the propranolol eye micro-drops treatment, as well as analyze corneal and vitreous transparencies, lens opacity, and regression of vessels in the tunica vasculosa lentis. The ROP progression will be monitored by indirect ophthalmoscopy using a 20D and 28D lens. The RetCam Imaging System will be systematically used by ophthalmologists to evaluate ROP evolution.

The timeline of the study is reported in Additional file 1.

All the adverse effects will be notified to the qualified responsible of pharmacovigilance, using the specified report form.

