### Intervention

All enrolled newborns will receive propranolol as ophthalmic solution (0.2%). Three micro-drops of 6 μL propranolol solution (= 6 μg propranolol/μ-drops) will be topically applied four times daily (every 6 h) in each eye with a calibrated pipette. After propranolol administration, the nasolacrimal duct will be carefully compressed for 1 min in order to decrease the percentage of drug absorbed by the conjunctival and nasal vessels. The treatment will be started as soon as the diagnosis of stage 1 ROP without plus is confirmed and will be continued until the complete development of retinal vascularization, but for no longer than 90 days. However, ophthalmologic exams will also be performed after this period to exclude possible rebound phenomenon. In these cases, propranolol eye micro-drops treatment will be resumed until retinal vascularization is completed.

The ophthalmologic approach for newborns enrolled in the study will be in accordance with the guidelines adopted by the ETROP Cooperative Group and the AAP/AAO/AAPOS guidelines [3, 66, 67]. The RetCam Imaging System will be systematically used by ophthalmologists to evaluate ROP evolution.

Eye drops will be prepared sterilely by diluting propranolol hydrochloride powder (ACEF, Fiorenzuola d’Arda, Piacenza, Italy), in sterile water for injection at a concentration of 2%. Then, the propranolol 0.2% solution will be obtained in a horizontal laminar flow hood adding 9 ml of saline solution to 1 ml of propranolol 2% preparation.

Newborns with ROP who progressed to stage 2 plus or stage 3 plus will be treated with laser photocoagulation or intravitreal anti-VEGF (bevacizumab) administration. The ophthalmologists will choose the treatment they will consider most appropriate.

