### Primary endpoint

-Number of infants who progress from ROP Stage 1 in zone II or III, without plus to Stage 2 with plus or Stage 3 with plus.-Analysis of propranolol plasma concentration at the steady state (on the tenth day of treatment).

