**Fig. 1 Fig1:**
[figure not shown]
Simon optimal two-stage design for phase II clinical trials

At the end of the study, if the overall cases of failure are less than 13 out of 96 newborns, the treatment with propranolol 0.2% eye drops will be considered effective in decreasing the rate of ROP progression to stage 2 or 3 with plus.

Additionally, considering the serious adverse effects observed in newborns receiving oral propranolol with plasma concentrations around 20 ng/mL, this value is currently considered a sort of safe cut-off value [55]. For this reason, if the mean propranolol plasma concentration will be less than 20 ng/ml, as expected, the treatment with propranolol eye drops should be considered safe, being unable to cause high plasma levels of propranolol.

The 96 preterm newborns will be enrolled approximately in 2–3 years. The enrokllment will be competitive: the individual centers participating in the trial will not have a predetermined number of patients to recruit, but they will compete with each other to recruit all expected patients. The trial will be completed when the last newborn enrolled has completed the treatment schedule or achieved final retinal vascularization.

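### With 6-hourly dosing, day-10 samples at 0, 2, 4 and 6 h repeat the trough and skip the first 2 h, so they cannot show that high plasma levels do not occur

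*Protocol article*

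**What the plan says.** - **Dosing (Intervention).** The drops "will be topically applied four times daily (every 6 h) in each eye". The tear duct is compressed for 1 minute after each dose "in order to decrease the percentage of drug absorbed by the conjunctival and nasal vessels".
- **Sampling (Data collection methods).** Levels are measured on dried blood spots "at the steady state on the 10th day of treatment, before administering therapy (T0), after 2 (T2), 4 (T4) and 6 h (T6").
- **Endpoint (Primary endpoint).** The second primary endpoint is "Analysis of propranolol plasma concentration at the steady state (on the tenth day of treatment"). No summary statistic is named there.
- **Safety conclusion (Experimental plan, text after Figure 1).** The criterion is "if the mean propranolol plasma concentration will be less than 20 ng/ml, as expected"; the treatment then "should be considered safe, being unable to cause high plasma levels of propranolol".
- **0.3% restart (Stop criteria and dose changes).** A restart at the higher concentration after failure on efficacy is conditional on plasma concentrations below 20 ng/mL. The word *mean* is not used.
- **Origin of the cut-off (Efficacy and safety of oral propranolol).** It comes from a mean level of around 20 ng/mL in infants on oral propranolol. The sampling times are not given.

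**The concern.** The conclusion is about high levels, but the sampling avoids the part of the interval where a high level would be expected if absorption is fast. The protocol itself names conjunctival and nasal vessels as a route of absorption and acts to limit it, yet takes no sample in the 2 h after instillation. Meanwhile two of the four spots measure the same trough.

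A sampling gap differs from an undefined summary statistic. A statistical analysis plan can specify a better average, but no analysis recovers a level that was never drawn. At stake is whether a primary safety endpoint can carry the statement made from it.

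**Working it through.** The 20 ng/mL figure is taken over from the oral trial, not calculated in the document, so there is no derived figure to reproduce.

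**Inputs from the article.** Dosing interval τ = 6 h; samples at 0 (pre-dose), 2, 4 and 6 h on day 10, stated to be steady state.

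**Assumptions (not in the article).** One compartment and first-order absorption; half-life 3, 4, 6, 9 or 12 h; single-dose time to peak (tmax) 0.25, 0.5 or 1 h, with 2 h as a further check.

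**Step 1: duplicate trough.** At steady state C(t) = C(t + τ), so C(0) = C(6) provided the 6 h spot precedes the next dose. This needs no assumed parameter.

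**Step 2: weights.**
- Plain mean of four samples: trough weight 2/4 = 50%.
- Trapezoid average: (C0/2 + C2 + C4 + C6/2)/3, so trough weight 1/6 + 1/6 = 33%. With C0 = C6 this equals the mean of C2, C4 and C6.

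**Step 3: size.** Up to a constant,

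C(t) = ka/(ka − ke) × [exp(−ke·t)/(1 − exp(−6ke)) − exp(−ka·t)/(1 − exp(−6ka))],

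with ke = ln 2/half-life, ka solved from ln(ka/ke)/(ka − ke) = tmax, and true interval average 1/(6ke).

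Worked corner, half-life 3 h and tmax 0.25 h (ke = 0.231, ka = 17.55 per h):
- C0 = C6 = 0.338, C2 = 0.851, C4 = 0.536.
- Plain mean = (0.338 + 0.851 + 0.536 + 0.338)/4 = 0.516.
- True average = 1/(6 × 0.231) = 0.721; ratio 0.516/0.721 = 0.715.
- Mean of C2, C4 and C6 = 0.575; ratio to the true average 0.797.

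| Half-life, tmax | Plain mean / true average | Trapezoid / true average | Plain mean / trapezoid | Peak / highest sample |
|---|---|---|---|---|
| 3 h, 0.25 h | 0.715 | 0.797 | 0.897 | 1.48 |
| 3 h, 1 h | 0.770 | 0.858 | 0.897 | 1.19 |
| 12 h, 0.25 h | 0.919 | 0.946 | 0.972 | 1.11 |
| 12 h, 1 h | 0.929 | 0.956 | 0.972 | 1.06 |
| 3 h, 2 h | 0.853 | 0.934 | 0.913 | 1.02 |
| 12 h, 2 h | 0.945 | 0.972 | 0.973 | 1.02 |

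For tmax of 0.25–1 h, the plain mean is therefore about 71–93% of the true average. Counting the trough twice lowers it by 3–10% (fourth column). The rest comes from the unsampled first 2 h, which time-weighting alone does not cure: the trapezoid reaches only 0.80–0.96. The unseen peak is 6–48% above the highest sample.

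**Step 4: wider range.** With half-life 1.5–15 h and ka 0.35–6 per h, the plain mean was below the true average in all 30 combinations (ratio 0.54–0.985), and the peak exceeded the highest sample by 0–89%. The direction of the bias in the mean is stable; its size is not.

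**The case against.** Several points against a stronger reading stand.

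- **The 0.3% restart.** A reader might infer that it turns on a trough-weighted mean. The text refers to concentrations, not a mean. If every sample must be below the cut-off, trough weighting does not arise there; only the unsampled window remains.
- **Levels at a severe event.** A reader might infer that an early severe reaction would coincide with an unmeasured level. The section on stop criteria provides for a dried-blood-spot level in exactly that case, and haemodynamic and respiratory parameters are monitored continuously for the first 3 weeks.
- **The plain mean.** The Experimental plan does not say that the four samples are pooled unweighted. A mean per time point or a time-weighted mean also fits, and the definition may sit in a fuller document. The 50% trough weight is one reading, not a stated rule.
- **The cut-off is itself a mean.** Setting a modelled peak against 20 ng/mL does not show a wrong safety call. If the oral reference was sampled in a similar way, part of the bias cancels. It is not shown that the rule is favourable by design.
- **No decision is shown to change.** The article reports levels consistently below the cut-off with 0.1% drops and gives no estimate for 0.2%.
- **The peak is missed only if it is early.** At a tmax of 2 h the loss is about 2%.

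These points limit size and reach. They do not supply a sample before 2 h, and they do not make a mean evidence about high levels.

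**Conclusion.** The point holds in a limited form. The stated schedule duplicates the trough and leaves the first 2 h after each dose unobserved, so it cannot support the inference that the drops are unable to cause high plasma levels. The duplication rests only on steady state and on the 6 h spot preceding the next dose.

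The size is conditional on a model and on parameters that the article does not give. It ranges from a material shortfall in the corner with a short half-life and fast absorption to a negligible missed peak when absorption is slow. The documents do not show that the safety conclusion would be wrong. This is a cheap improvement to a primary endpoint, not a defect that invalidates the trial.

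**What to change.** 1. Keep four blood spots, but move one of the two trough draws (0 or 6 h) to within the first hour after the dose. In the same model (half-life 3–12 h, tmax 0.25–1 h), use the remaining trough at both ends of the interval and an early draw at time e. The trapezoid is then [e(C0 + Ce)/2 + (2 − e)(Ce + C2)/2 + (C2 + C4) + (C4 + C6)]/6. It gives about 0.97–0.99 of the true average for e = 0.5 h and 0.91–0.98 for e = 1 h.
2. Report a time-weighted interval average, to set beside the mean-based 20 ng/mL reference, together with the highest observed individual level.
3. If the schedule stays, limit the conclusion in the Experimental plan to the times sampled.
4. Reconcile the wording of the 20 ng/mL criterion between the Experimental plan (mean) and the section on stop criteria and dose changes (concentrations).

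Cost: an amendment and a change to the laboratory instructions, with the same number of spots, blood volume and assays. The real loss is the duplicate trough, which is the schedule's built-in check that day 10 is at steady state; using one trough at both ends of the interval then rests on that premise untested. Items 2 to 4 need wording only.

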### Statistical methods

#### Preliminary analysis

To plan the present multicenter, open-label, single arm, phase II trial, a preliminary analysis was performed to evaluate historical ROP incidence in the 6 NICUs involved in the study.

This analysis included all preterm newborns admitted to the NICUs contributing to the study (Florence, Milan, Monza, Siena, Varese, Brescia) and diagnosed with any stages of ROP from 2011 to 2015. During the 5 years preceding the present study, 248 patients out of 2165 very low birth weight newborns (11.5%) were diagnosed with ROP. Demographic and obstetric characteristics of this historical cohort are reported in Table 1. However, only 237 of these newborns (95.6%) shared the same enrollment criteria of this planned trial. In fact, 3 newborns were suffering from AP-ROP and 8 newborns showed a ROP ≥ stage 2 at first examination. Therefore, in Table 1 we also show the demographic and obstetric characteristics of these 237 newborns who showed ROP stage 1 at first examination.

**Table 1 Tab1:** Demographic and obstetric characteristics of historical cohort, co-morbidities and co-interventions

Demographic and obstetric characteristics	Any stage ROP	Stage 1 ROP at first visit
Newborns*, n* (%)	248	237 (95.6)
Gestational age, weeks, *mean ± SD*	26.6 ± 2.0	26.7 ± 2.0
Birth weight, g, *mean ± SD*	838 ± 233	843 ± 235
Male, *n* (%)	129 (52.0)	126 (53.2)
Caesarean delivery, *n* (%)	170 (68.5)	162 (68.3)
Stained amniotic fluid, *n* (%)	18 (7.3)	16 (6.7)
Apgar Score, 1 min, *mean ± SD*	4.6 ± 2.3	4.6 ± 2.3
Apgar Score, 5 min, *mean ± SD*	7.4 ± 1.7	7.4 ± 1.7
Post menstrual age at diagnosis, weeks, *mean ± SD*	34.1 ± 2.2	34.2 ± 2.3
Co-morbidities and co-intervention		
Respiratory distress syndrome, *n (%)*	239 (96.4)	228 (96.2)
Surfactant treatment, n (%)	208 (83.9)	198 (83.5)
Duration of oxygen exposure (days), *median (range)*	49.4 (0–291)	46.7 (0–291)
Bronchopulmonary dysplasia ^a^, *n* (%)	170 (68.5)	160 (67.5)
Candida sepsis, *n* (%)	12 (4.8)	12 (5.1)
Other sepsis, *n* (%)	143 (57.7)	132 (55.7)
Number of red blood cell transfusions, *median (range)*	5 (0–19)	5 (0–19)
Intraventricular hemorrhage, grade 3–4, *n* (%)	40 (16.1)	38 (16.0)
Post-hemorrhagic hydrocephalus, *n* (%)	17 (6.8)	15 (6.3)
Cholestasis, *n* (%)	66 (26.6)	60 (25.3)
Necrotizing enterocolitis, *n* (%)	32 (12.9)	31 (13.1)
Gastrointestinal perforation, *n* (%)	26 (10.5)	25 (10.5)
Surgical closure of patent ductus arteriosus, *n* (%)	56 (22.6)	52 (21.9)
Survival, n (%)	245 (98.8)	234 (98.7)

A total of 63 newborns out of 248 diagnosed with any stage of ROP (25.4%) showed a stage 2 or 3 with plus and received a treatment (Table 2). The same analysis was repeated excluding the three newborns suffering from AP-ROP, and the eight newborns who showed a ROP stage ≥2 at first examination. Regarding the 237 newborns that showed ROP stage 1 at first examination, 58 (24.5%) progressed from stage 1 to stage 2 or 3 with plus. Overall, 45 newborns underwent laser photocoagulation, while 27 newborns were treated with bevacizumab administration (14 newborns, in fact, received both treatments). Four patients progressed to stage 4 ROP and were treated with vitrectomy (one also with cryotherapy). Finally, one newborn progressed to stage 5 ROP. These data were used to plan the current prospective study.

**Table 2 Tab2:** Ophthalmologic outcome of historical cohort

ROP progression	Any stage ROP	Stage 1 ROP at first visit
Newborns*, n* (%)	248	237 (95.6)
Aggressive Posterior ROP, *n* (%)	3 (1.2)	
Stage ≥2 at first examination, *n* (%)	8 (3.2)	
Stage 1 ROP at first examination, *n* (%)	237 (95.6)	
Stage 2, *n* (%)	172 (69.3)	165 (69.6)
Stage 3, *n* (%)	72 (29.0)	68 (28.7)
Stage 2 or 3 ROP with plus, *n* (%)	63 (25.4)	58 (24.5)
Stage 4 ROP, *n* (%)	4 (1.6)	4 (1.7)
Stage 5 ROP, *n* (%)	1 (0.4)	1 (0.4)
Treatment with laser photocoagulation, *n* (%)	47 (18.9)	45 (19.0)
Treatment with bevacizumab, *n* (%)	30 (12.1)	27 (11.4)
Vitrectomy, *n* (%)	4 (1.6)	4 (1.7)
Cryotherapy, *n* (%)	1 (0.4)	1 (0.4)

### Endpoint

For the present multicenter, open-label, single arm, phase II trial, the following endpoint will be evaluated:

### Primary endpoint

-Number of infants who progress from ROP Stage 1 in zone II or III, without plus to Stage 2 with plus or Stage 3 with plus.-Analysis of propranolol plasma concentration at the steady state (on the tenth day of treatment).

### Secondary endpoint

-Number of infants who progress to Stage 2 without plus ROP.-Number of infants who progress to Stage 3 without plus ROP.-Number of infants who progress to Stage 4 or 5 ROP with total or partial retinal detachment.-Number of infants who need vitrectomy.-Number of adverse events due to propranolol eye drops treatment.

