**Methods:**

A multicenter, open-label, phase II, clinical trial, planned according to the Simon optimal two-stage design, will be performed to analyze the safety and efficacy of propranolol 0.2% eye micro-drops in preterm newborns with stage 1 ROP. Preterm newborns with a gestational age of 23–32 weeks, with a stage 1 ROP will receive propranolol 0.2% eye micro-drops treatment until retinal vascularization has been completed, but for no longer than 90 days. Hemodynamic and respiratory parameters will be continuously monitored. Blood samplings checking metabolic, renal and liver functions, as well as electrocardiogram and echocardiogram, will be periodically performed to investigate treatment safety. Additionally, propranolol plasma levels will be measured at the steady state, on the 10th day of treatment. To assess the efficacy of topical treatment, the ROP progression from stage 1 ROP to stage 2 or 3 with plus will be evaluated by serial ophthalmologic examinations.

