#### Efficacy and safety of oral propranolol

The studies in the OIR model provided a considerable amount of results which strongly indicate that β2-AR blockade may play a significant action against hypoxia-induced retinal neovascularization. This evidence prompted an interest in exploring the possibility that the administration of propranolol may not only be used to treat IH but also be of help in the treatment of ROP. A randomized controlled trial [56] was performed to verify the efficacy and safety of oral propranolol in preterm newborns (GA < 32 weeks) with ROP stage 2 without plus in zone II [57]. Oral propranolol significantly decreased ROP progression to both stage 3 and stage 3 with plus, and none of treated newborns progressed to stage 4. The number of newborns who underwent laser photocoagulation or bevacizumab administration was significantly lower in the treated group [56]. These data are consistent with those reported by other authors [58–60]. Despite propranolol being generally safe and well tolerated in infancy, serious adverse events have been reported in unstable preterm newborns, mainly in conjunction with other conditions, such as sepsis, anesthesia or tracheal stimulation [56]. In these patients receiving the lower dose of 1 mg/kg/day, mean propranolol plasma concentration was around 20 ng/mL. Considering that pharmacological effects of β-blockers are usually related to the plasma concentrations, it appears prudent to avoid in future clinical trials propranolol concentrations higher than 20 ng/mL, that was considered a sort of safe cut-off value [56]. Although propranolol is effective in counteracting ROP progression [56, 58–60], the incidence of adverse events indicates that systemic administration is not sufficiently safe in preterm newborns [56]. Recently, also prophylactic propranolol administered on seventh day of life showed a decreasing trend in the incidence of ROP, need for laser therapy, and treatment with anti-VEGF [61].

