### Trial design

The present study is a multicenter, open-label, single arm phase II trial planned as a Simon optimal two-stage design [65], under the hypothesis that the treatment decreases the incidence of ROP progression to stage 3 with plus (estimated from historical data to be at least 19%) by 50% or more.

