### Modification

#### Stop criteria and dose changes

Considering that unstable newborns (i.e. after anesthesia induction) have shown a high risk of adverse events (hypotension and bradycardia) due to propranolol administration, whenever surgery and/or anesthesia are indicated, the discontinuation of the propranolol eye micro-drops treatment is recommended at least 24 h before.

Newborns in whom propranolol administration will be temporarily suspended for more than two doses, with the exception of a temporary suspension before surgery will be excluded from the study.

In the case of a severe adverse event (bradycardia, bronchospasm, severe hypotension or severe local signs) due to propranolol eye micro-drops therapy, the treatment will be promptly stopped and the newborn will be excluded from the study. The concentration of propranolol will be measured on dried blood spots to verify the relationship between the adverse event that occurred and the plasmatic levels of propranolol. Moreover, after the first adverse event, the study could be restarted reducing the propranolol eye drops dosage to two micro-drops of 6 μL 0.2% propranolol solution administered four times daily in each eye. An additional enrolment phase will be opened and will be based on a new study population not including newborns previously treated.

Similarly, the study could be restarted increasing the concentration of propranolol eye drops solution up to 0.3% in case of treatment failure in terms of efficacy during the first stage of the study, if plasma propranolol concentrations are below the cut off of 20 ng/ml.

The outcomes of infants who develop adverse effects to propranolol will be reported to Pharmacovigilance Center and then published.

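### The only adverse event endpoint counts events judged due to the drops, so in an open-label single-arm trial drug-related harm can be ascribed to another cause and left out

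*Protocol article*

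**What the plan says.** Trial design: "The present study is a multicenter, open-label, single arm phase II trial planned as a Simon optimal two-stage design". The primary objective names safety together with efficacy.

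Two listed endpoints carry safety:
- Primary endpoint: propranolol plasma concentration at steady state, on the tenth day of treatment.
- Secondary endpoint: "Number of adverse events due to propranolol eye drops treatment".

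The remaining endpoints concern ROP progression and vitrectomy. None counts adverse events whatever their cause. Under Experimental plan, the drops are to be considered safe if the mean plasma concentration is below 20 ng/ml. That rule has no clinical event criterion.

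On the drug's known harms, Efficacy and safety of oral propranolol states that "serious adverse events have been reported in unstable preterm newborns, mainly in conjunction with other conditions, such as sepsis, anesthesia or tracheal stimulation". Stop criteria and dose changes adds that unstable newborns, for example after induction of anaesthesia, "have shown a high risk of adverse events (hypotension and bradycardia) due to propranolol administration". Its rule for severe events carries the same attribution condition as the endpoint: "due to propranolol eye micro-drops therapy, the treatment will be promptly stopped and the newborn will be excluded from the study".

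On observation, Data collection methods states: "Hemodynamic parameters, diuresis and respiratory parameters will be continuously monitored during the first 3 weeks of treatment". Laboratory tests, electrocardiogram and echocardiogram are weekly over the same 3 weeks. Under Intervention, treatment runs until retinal vascularization is complete, with a cap of 90 days.

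**The concern.** The endpoint applies a causality judgement before an event is counted. With no control arm, drug-caused events cannot be separated from background events by comparing groups, and with no masking the judgement is made by people who know the treatment. The article's own background describes harms that arise mostly when another explanation is present. In that setting a causality filter can remove the events the trial most needs to see.

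At stake is the clinical half of the safety objective. The plasma rule can declare the drops safe whatever happens to the infants, so the adverse event endpoint is where a conflicting clinical signal would have to appear. If it is filtered, a low count cannot be told apart from a low rate of attribution. The count also combines a period of continuous monitoring with later treatment under lighter observation.

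**Working it through.** **The plan's own figures.** No figure is stated for the adverse event endpoint. The stated efficacy design does reproduce: with failure rates of 19% and 9.5%, an exact search for Simon's optimal design returns 37 then 96 newborns, failing at 6 or more of 37 or at 13 or more of 96, with one-sided alpha 0.0493 and power 0.802. This point does not touch that design.

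**The sections side by side.**
1. Secondary endpoint admits an event only if it is judged due to the drops.
2. Trial design gives neither masking nor a comparator, so that judgement has no check within the trial.
3. Efficacy and safety of oral propranolol places the drug's serious events mainly alongside competing causes.
4. Experimental plan declares safety on a mean concentration, so it cannot bring back an event that was ascribed elsewhere.
5. Stop criteria and dose changes provides a drug level after a severe event, but the event has already been called due to the drops by then. Events ascribed to another cause do not reach this step.

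From 1 to 3, a drug-related event can be left out of the endpoint. From 4 and 5, nothing else in the listed endpoints or rules would recover it.

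**Illustration of size, on assumed inputs.** Let *h* be the proportion of infants with a truly drug-related event and *s* the share of those ascribed to another cause. Neither is given in the document.
- Expected infants counted = 96 × *h* × (1 − *s*)
- Chance that none is counted = (1 − *h*(1 − *s*))^96

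| *h* | *s* | Truly affected | Counted | Chance of counting none |
|---|---|---|---|---|
| 5% | 0 | 4.8 | 4.8 | 0.7% |
| 5% | 25% | 4.8 | 3.6 | 2.6% |
| 5% | 50% | 4.8 | 2.4 | 8.8% |
| 5% | 75% | 4.8 | 1.2 | 29.9% |
| 10% | 25% | 9.6 | 7.2 | 0.1% |
| 10% | 50% | 9.6 | 4.8 | 0.7% |
| 10% | 75% | 9.6 | 2.4 | 8.8% |

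The table shows how sensitive the count is to attribution. It does not estimate what will happen.

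**Observation period.** Continuous monitoring covers 21 days. For an infant treated to the cap this is 21/90 = 23% of treatment time. For shorter treatment the share is larger, so 23% is the lowest value.

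**The case against.** Several objections have force.

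- **Direction of bias.** Staff who know that every infant receives a beta-blocker could also over-attribute. The article itself calls hypotension and bradycardia around anaesthesia a consequence of propranolol, so its authors have attributed events to the drug despite a competing cause. This stands: undercounting is possible, not certain.
- **Route.** The pattern with sepsis and anaesthesia comes from oral dosing. The section on the 0.1% drops reports no adverse effects and plasma levels consistently below 20 ng/mL, and stopping the drops before surgery or anaesthesia is recommended. This lowers the expected number of events. It does not make an attributed count a sound measure of them, and the Discussion says that this trial raises both dosage and concentration.
- **Sepsis rate.** A reader might take the 55.7% of the historical stage 1 cohort with sepsis other than Candida (Table 1) as the share of events that will be misattributed. The document does not support that. The figure carries no timing. Mean post-menstrual age at diagnosis was 34.2 weeks and mean gestational age 26.7 weeks, a difference of 7.5 weeks, so some of that sepsis may precede any treatment.
- **Monitoring.** A reader might see a contradiction between the abstract, "Hemodynamic and respiratory parameters will be continuously monitored", and the 3-week limit in Data collection methods. The abstract only condenses the fuller text. Nor is later treatment unobserved, since ophthalmologic examinations, which check for local adverse events, are not confined to 3 weeks.
- **Comparison with other cohorts.** Table 1 gives no rates of bradycardia or hypotension, so an all-cause count would not yield a historical comparison either. No such gain is claimed here.
- **Full protocol.** Causality criteria or an all-event listing may exist there. The endpoint is nevertheless stated in the article, and it is stated as restricted.

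**Conclusion.** The point holds as a weakness in how the endpoint is defined. The only clinical safety endpoint depends on unmasked attribution without a comparator, for a drug whose serious events by the oral route came mainly alongside other plausible causes. Drug-related events can therefore be missed. Because safety is declared on mean plasma concentration alone, no other listed endpoint could show clinical harm that conflicts with that conclusion.

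The size of any undercount cannot be derived from the document, and the figures in the table rest entirely on assumed values of *h* and *s*. A reader might infer that harms will be attributed elsewhere, or that a near-zero count would by itself lead to a declaration of safety. The document supports neither: the first is a risk only, and the stated safety rule gives the event count no decision role. The efficacy design is unaffected. The change is worth making before analysis, because it keeps the planned count and removes its dependence on a judgement that cannot be checked.

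**What to change.** Replace the adverse event endpoint under Secondary endpoint with wording such as: *Number and proportion of treated infants with any adverse event during treatment, overall and by type (bradycardia, hypotension, bronchospasm, local ocular signs, other), regardless of attribution. Infants with events judged due to propranolol are reported as a subset.*

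Tabulate events in the first 3 weeks of treatment separately from later events, each against the number of infants under treatment in that period. Keep infants withdrawn after an event in both numerator and denominator.

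The costs are a higher and less favourable count that includes background events of prematurity, one more table, and possibly a case report form field for all-cause events after day 21, since the article does not say that these are recorded. Sample size, the efficacy rules and clinical management need no change.
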